#### Follow-up of patients who withdraw from the study

Any patients whose treatment is withdrawn will continue to be followed until the event in question is resolved or until, in the researcher’s opinion, important changes in the patient’s health state are unlikely to occur. The follow-up reports at 15, 30, 60 and 90 days will be completed for all patients who received medication (including placebo) during this study.

#### Suspension of the study

In cases where severe adverse events related to the administration of the treatment are suspected, the study shall be interrupted and the researchers and the coordinator will decide whether to continue or otherwise. Ultimate responsibility for this decision will rest with the coordinator. The relevant clinical research ethics committees and the health-care authorities shall be informed of any decisions taken to interrupt, abandon or continue the study.

### Ethical criteria

#### Applicable regulations

The study will be carried out in accordance with the principles of the Helsinki Declaration, specifically the European Medicines Agency Committee for Proprietary Medicinal Products (EMEA/CPMP) declaration on the use of a placebo in clinical trials, and in accordance with the guideline for good clinical practice (CPMP/ICH/135/95, 17 July 1996), as well as local regulations.

#### Recruitment

The study protocol was approved by the regional clinical trial committee, the ethics committee of the University Regional Hospital (Malaga, Spain) and the Spanish Agency of Medicines and Medical Devices. Implementation of the study will start after the Spanish national health-care authorities give their formal approval. Although patients are to be informed that they are free to abandon the study at any time, we shall seek to recruit those offering the maximum probability of remaining within the study until its conclusion.

#### Informed consent for minors

After identifying candidate patients for inclusion in the clinical trial, the children will be given an oral and written explanation of the study. The parents and/or guardians will be provided with all available information and any complementary information they may require, and they will be given an information sheet so that their informed consent for the children’s participation in the trial may be obtained. Once this form has been signed, it should be given to the researcher when the child attends the clinic for the baseline evaluation (t0).

#### Liability for injury

According to the Spanish law regarding clinical trials, an insurance policy for civil liability must be subscribed to cover any injuries that may arise from the conduct of the study.

### Treatment details

#### Dosage and administration of medication

The medication used in the trial will be administered orally at the patients’ homes. The medications provided will be tocopherol acetate 10 mg/kg/day, administered in two daily doses, and ascorbic acid 10 mg/kg/day, administered in two daily doses.

#### Preparation and labelling of treatment procedures

The medications used in the trial will be prepared, labelled and stored by the pharmacy service at the Virgen de las Nieves Hospital (Granada, Spain). The active principles of the treatment group will be obtained via commercially available drugs. The placebo used will be created in the hospital’s pharmacy department and will emulate the excipients and volume of the experimental medication. Procedures for reducing the volume of medication per pack will be implemented in accordance with International Conference on Harmonisation requirements. The study coordinator will supervise all procedures applied in this respect. Double-blinding and randomization of patients in the two groups will be carried out by the pharmacy service at the Virgen de las Nieves Hospital (Granada, Spain).

#### Other medications allowed

The patients will continue taking their usual medication to control symptoms or associated comorbid pathologies. Moreover, they will continue receiving any preexisting psychological or educational therapies. In addition, they will continue taking any medication prescribed for any other concurrent illness prior to their entering the study.

### Specific methods

#### Evaluation of effectiveness

The clinical evaluation of the patients will be carried out by utilising the CPRS-R) [57] and the CTRS-R [58]. These scales have been validated for the study of hyperactivity in children. The Conners score is applied by means of a structured questionnaire with multiple informants (generally parents and teachers) who assess the child’s behaviour over a period of at least 1 month. The translation into Spanish and its adaptation to local conditions were previously validated [59].

#### Measurement instruments

The Spanish version of the CPRS-R will be used. Scoring on this scale ranges from 0 to 100 points (T-score). A T-score of 50 or more on the CPRS-R at t0 will be considered a cutoff for the inclusion of patients in the study.

The Spanish version of the CTRS-R will be used. Scoring on this scale ranges from 0 to 100 points.

The DBC-P24 will be used [60]. The Spanish version of the DBC-P24 (90) was used to identify the degree of behavioural difficulties among participants. Each behavioural description is scored with a 0, 1 or 2 rating, where 0 = ‘not true as far as you know’, 1 = ‘somewhat or sometimes true’ and 2 = ‘very true or often true’. The tally provides a total score.

Completed PGWBI-R (Spanish version) forms will be obtained from parents at the beginning and the end of the study in order to assess the psychological repercussions of the treatment on family life. This scale reflects subjective feelings and psychological well-being (or otherwise) during the previous week [61].

Oxidative stress status in blood will be assessed at t0, t1 and t2 to detect metabolic changes that may be related to the effectiveness of the treatment. Qualitative changes in the metabolism and antioxidant levels will be evaluated.

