#### Instrumentation

The clinical data and the results of the Wechsler Intelligence Scale for Children–Revised (WISC-R), the Conners Parent Rating Scale–Revised: Long Form (CPRS-R) [57], the Conners Teacher Rating Scale–Revised: Long Form (CTRS-R) and the Developmental Behaviour Checklist Short Form (DBC-P24) will be assessed at the baseline of the clinical condition (t0), at an intermediate time point after 12 weeks of treatment (t1) and at the end of the experimental period after 24 weeks of treatment (t2). The parents and/or guardians will be informed about the study details, and, upon receipt of their informed consent, the previously randomized medication will be provided. The medication is to be taken at the patient’s home, and a phone call follow-up is to be performed by the same neuropsychologist in charge of the evaluation at 30, 60, 120 and 150 days. Blood tests will be performed at the start (t0), intermediate time point (t1) and at the end of the experimental period (t2) for each of the 30 patients. The psychological impact of the treatment on the families concerned will be measured using the Spanish version of the Psychological General Well-Being Index–Revised (PGWBI-R).

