#### Safety evaluation

The following evaluations will be performed before and after the treatment:Haematology: haemoglobin, haematocrit, red blood cells, white blood cells and plateletsBiochemistry: creatine, blood urea nitrogen, glucose, uric acid, sodium, potassium, calcium, phosphate, chloride, total protein, albumin, triglycerides, total cholesterol, high-density lipoprotein, total bilirubin, aspartate aminotransferase (serum glutamic oxaloacetic transaminase), alanine transaminase (ALT; serum glutamic pyruvic transaminase), γ-glutamyl transpeptidase, alkaline phosphatase, cAMP, glutamic acid and pyruvic acidHypothalamic-pituitary-adrenal axis (adrenaline, noradrenaline, dopamine, cortisol, adrenocorticotropic hormone)Other tests Hormones (luteinizing hormone, follicle-stimulating hormone, growth hormone, thyroid-stimulating hormone and thyroid hormone)Neurotransmitters (serotonin, γ-aminobutyric acid (GABA))cAMPVitamins (vitamins A, C and E)Ceruloplasmin, albumin and transferrinMinerals (selenium, zinc, copper and manganese)amino acids in serumAnalysis of urine density, pH, protein, glucose, ketone bodies, bilirubin, blood, nitrite, urobilinogen, leukocytes, urinary sediment, sodium, chlorine and potassium

The following medical parameters will be evaluated in the enrolled patients:Heart symptoms: mitral valve prolapseNeurological symptoms: epilepsyMotor symptoms: hypotonia, fine and gross motor delay, stereotypes and hyperextensible finger jointsMorphological features: macroorchidism, scoliosis, hyperpigmentation of the skin, otitis, strabismus and macrocephaly

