NCT00895752	Phase IV single centre	Riluzole	Adults	Inhibitor of glutamate release	Completed	Indiana University (USA)	[66]
NCT01254045	Phase II single centre	Oxytocin	Adolescents and adults	Social brain neuropeptides	Completed	Stanford University (USA)	[67]
NCT01120626	Open label	Donepezil	Adolescents and children	Cholinergic drug	Completed	Stanford University (USA)	[68]

^a^GABA, γ-aminobutyric acid; GABA-B, γ-aminobutyric acid; mGluR5, metabotropic glutamate receptor 5; NMDA, *N*-methyl-D-aspartate.

FMRP is an mRNA-binding protein that is important for mRNA transport, mRNA stabilization and translation regulation of mRNA into protein at the synapse [69]. FMRP is also a factor in the regulation of brain oxidative stress, so, in the absence of FMRP, there is hyperactivation of Rac1-GTPase-dependent NADPH-oxidase signalling. These alterations lead to an excess of free radical production that, in the long term, produces oxidative stress, which is a crucial factor in the central nervous system that disrupts neuron, astrocyte and microglia communication [32]. Evidence of oxidative stress in FXS is manifested by high levels of oxidised proteins, lipid peroxidation end products, formation of carbonyls and oxidative alteration of the glutathione system in the brain of the *Fmr1*-knockout mouse model [21].

Since 1983, it has been indicated that vitamins can improve FXS patients’ cognitive status. The first vitamin used for the treatment of the FXS was folic acid. Several publications describe the efficacy and safety of treatment with folic acid in people with FXS [70–73].

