The reason for performing blood and urine tests in our experimental group at t0, t1 and t2 is to corroborate the general safety of the treatment and to improve antioxidant blood status, as well as to reveal any alterations occurring in these parameters as a result of the medication administered. Nevertheless, it seems reasonable to support the results of the clinical evaluation with objective data such as blood tests. It is also important to assess the repercussions on family life (which tend to be greatly impaired in severe cases) of an improvement in the control of FXS symptoms among children. The PGWBI reflects psychological well-being (or otherwise); it is based on theories of evaluation of the domestic environment and is an appropriate means of determining the distortion produced by FXS within the household. We have no doubt that a direct correlation will be found between the children’s symptoms and psychological well-being within the family home.

The combined application of these three measurement methods—namely, the objectification of FXS symptoms and incapacity, the assessment of metabolic blood and urine changes and the evaluation of stress within the family—will enable us to reach an objective judgment of the effectiveness of the treatment being tested.

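### The blood results are given a supporting role for effectiveness, but they are to be read qualitatively, include the administered vitamins, and have an inconsistently stated sampling plan

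*Protocol article*

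**What the plan says.** **Purpose and reading rule.** Under Measurement instruments, blood oxidative stress status is measured at t0, t1 and t2, in order to pick up metabolic changes that could relate to whether the treatment works. The next sentence gives the only reading rule: "Qualitative changes in the metabolism and antioxidant levels will be evaluated".

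**What is measured.** Measurement instruments names no analyte. The only analyte list is under Safety evaluation, and it contains vitamins A, C and E among many other tests. Under Dosage and administration of medication, the products given are tocopherol acetate and ascorbic acid, that is, vitamins E and C.

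**How the results will be used.** The Discussion gives improvement of antioxidant status in blood as one reason for the tests and adds that "it seems reasonable to support the results of the clinical evaluation with objective data such as blood tests". It then says of symptoms, blood and urine changes, and family stress: "The combined application of these three measurement methods" "will enable us to reach an objective judgment of the effectiveness of the treatment being tested".

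**Who is sampled, and when.** Instrumentation schedules blood at three times, the last "at the end of the experimental period (t2) for each of the 30 patients". Study periods schedules blood and urine tests for included patients at the same three times. Safety evaluation introduces its list with "The following evaluations will be performed before and after the treatment". The Discussion speaks of "The reason for performing blood and urine tests in our experimental group at t0, t1 and t2".

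**The concern.** Blood values are offered as objective support for a result that otherwise rests largely on ratings by parents and teachers. Support of that kind needs a measure that can move independently of simply taking the product, a comparison with placebo, and a stated way of reading the change. The text falls short on each:

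- Two of the three listed vitamins are the study products. Their levels would be expected to rise in treated boys even if the treatment did nothing for oxidative stress or behaviour.
- A qualitative reading of measured concentrations gives no size of effect and leaves room for judgement after the data are seen.
- The sampling statements disagree, so the set of samples behind any comparison is not fixed by the text.

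At stake is a report in which higher vitamin levels are presented as better antioxidant status and then cited as corroboration of a clinical effect.

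**Working it through.** The point depends on no sample size or power figure, so the check is a comparison of sections.

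**1. Is there a quantitative rule for blood?** General considerations names between-group comparisons for the CPRS-R, the CTRS-R and the DBC-P24, and applies the same analysis to the well-being index. It defines the principal outcome as the baseline-adjusted change in Conners score. Blood measures appear in none of these sentences. What could reach them is the general statement that quantitative variables are summarised by centre and spread within each arm. That is a description, not a comparison of change. The only sentence specific to blood is the qualitative one in Measurement instruments.

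**2. Can the named antioxidants show an effect rather than exposure?**

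| Listed vitamin | Given as study product? | What a rise shows |
|---|---|---|
| A | No | Not explained by direct dosing |
| C | Yes (ascorbic acid) | Intake and absorption |
| E | Yes (tocopherol acetate) | Intake and absorption |

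The Safety evaluation list also has ceruloplasmin, albumin, transferrin, uric acid, bilirubin and trace minerals, so vitamins C and E are not the only entries connected with antioxidant status. However, no section separates exposure measures from response measures. A rise in C and E could therefore be counted as improved antioxidant status.

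**3. Do the sampling statements agree?**

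| Section | Who | When |
|---|---|---|
| Instrumentation | Each of the 30 patients | t0, t1, t2 |
| Study periods | Included patients | t0, t1, t2 |
| Safety evaluation | Enrolled patients, by context | Before and after treatment; t1 not mentioned |
| Discussion | Experimental group | t0, t1, t2 |

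General considerations contrasts experimental with control, and so does an earlier paragraph of the Discussion. Read literally, the Discussion phrase therefore means the active arm. The two operative methods sections include everyone, so it is probably loose wording.

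**4. How much weight does blood carry?** The Discussion credits the judgment of effectiveness to three methods together. The metabolic aim is secondary and descriptive in both the Abstract and the opening of Methods/Design. No decision rule in the article depends on a blood value.

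**The case against.** The best reply is that little rests on blood. Effectiveness is formally judged on the Conners change, the metabolic aim is only to describe, and blood is there to support the clinical evaluation. General considerations already summarises quantitative variables by arm, and formal analysis of exploratory laboratory values usually sits in the analysis plan. The article's hypothesis also includes a vitamin deficit, so vitamin levels are of interest in themselves.

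Much of this stands and limits the severity. It does not remove the point. The qualitative reading is a stated choice rather than an omission, and it sits badly with calling the results objective data. Correcting a vitamin deficit is still exposure: it does not show lower oxidative stress or better behaviour.

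Three stronger readings are tempting, and the document does not support them:

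- *That no marker of oxidative damage is measured.* The article describes oxidative stress in the knockout mouse brain by "high levels of oxidised proteins, lipid peroxidation end products, formation of carbonyls and oxidative alteration of the glutathione system", and none of these is in the Safety evaluation list. But that is a safety list in a condensed article, and oxidative stress status is promised separately. The assays may be named in the full protocol, which is not shown.
- *That only the active arm is sampled, which would remove the placebo comparison and reveal allocation.* This rests on one Discussion phrase, against two methods sections that include all patients.
- *That the 12-week panel is lost.* Safety evaluation does not say that tests are done only before and after treatment, and t1 tests are scheduled elsewhere.

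**Conclusion.** The point holds in a limited form. As written, the blood results do not justify the supporting role for effectiveness that the Discussion gives them: their specific reading rule is qualitative, no between-arm comparison is named, and the listed antioxidants include both administered vitamins with nothing to set them apart as exposure. Separately, the sampling statements conflict on timing and on the group sampled and need to be reconciled.

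The size is modest. The principal analysis is unaffected, and the consequence is a possible over-reading of a secondary, descriptive result. It would go too far to say that the blood data cannot contribute to a judgment of effectiveness, because a suitable measure may be specified in the unshown protocol. The verdict assumes that vitamin C and E levels respond to intake, which the article does not quantify, and that the vitamins listed under Safety evaluation are among the antioxidant levels meant under Measurement instruments.

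**What to change.** 1. In Measurement instruments, replace the qualitative reading with the between-arm difference in change from t0, adjusted for the t0 value and reported with its confidence interval as a secondary exploratory result. This is the form already used for the principal outcome, applied to values already scheduled for collection.
2. State that plasma vitamins C and E are exposure or adherence measures and do not count toward effectiveness.
3. In the Discussion, limit the effectiveness claim for blood to any oxidative-stress measure actually assayed, or drop the claim. No new assay is asked for.
4. Reconcile Safety evaluation and the Discussion with Instrumentation and Study periods, so that one timing is stated for the listed panel and it is clear that both arms are sampled.

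The cost is changes of wording and a short added analysis. The downside is a weaker stated claim for the blood data.

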#### Safety evaluation

The following evaluations will be performed before and after the treatment:Haematology: haemoglobin, haematocrit, red blood cells, white blood cells and plateletsBiochemistry: creatine, blood urea nitrogen, glucose, uric acid, sodium, potassium, calcium, phosphate, chloride, total protein, albumin, triglycerides, total cholesterol, high-density lipoprotein, total bilirubin, aspartate aminotransferase (serum glutamic oxaloacetic transaminase), alanine transaminase (ALT; serum glutamic pyruvic transaminase), γ-glutamyl transpeptidase, alkaline phosphatase, cAMP, glutamic acid and pyruvic acidHypothalamic-pituitary-adrenal axis (adrenaline, noradrenaline, dopamine, cortisol, adrenocorticotropic hormone)Other tests Hormones (luteinizing hormone, follicle-stimulating hormone, growth hormone, thyroid-stimulating hormone and thyroid hormone)Neurotransmitters (serotonin, γ-aminobutyric acid (GABA))cAMPVitamins (vitamins A, C and E)Ceruloplasmin, albumin and transferrinMinerals (selenium, zinc, copper and manganese)amino acids in serumAnalysis of urine density, pH, protein, glucose, ketone bodies, bilirubin, blood, nitrite, urobilinogen, leukocytes, urinary sediment, sodium, chlorine and potassium

The following medical parameters will be evaluated in the enrolled patients:Heart symptoms: mitral valve prolapseNeurological symptoms: epilepsyMotor symptoms: hypotonia, fine and gross motor delay, stereotypes and hyperextensible finger jointsMorphological features: macroorchidism, scoliosis, hyperpigmentation of the skin, otitis, strabismus and macrocephaly

#### Reporting of adverse events

Any adverse events reported spontaneously by the subject or observed by the researcher or the research team will be recorded on the form designed for this purpose. The researcher will classify the intensity of said adverse events in accordance with the following scale:*Mild*: some discomfort, but not such as to interrupt normal daily activity*Moderate*: sufficient discomfort to reduce or notably affect normal daily activity*Severe*: causing incapacity to work or perform normal daily activities

The periodicity of the event shall be classified in accordance with the following scale:*Single occurrence*: just one event of limited duration*Intermittent*: various episodes of an event, each of limited duration*Persistent, unlimited*: an event that has persisted over time and is of indefinite duration

For each adverse event, its relation to the medication taken (definitive, probable, possible, improbable, none), in the researcher’s opinion, as well as any action taken as a result, will be recorded on the data collection form. The occurrence of an adverse event that is fatal, potentially fatal or incapacitating, or that requires or prolongs hospitalization, or that provokes severe congenital anomalies will be recorded as a ‘severe’ adverse event (SAE).

All SAEs and unexpected adverse pharmacological reactions, defined as adverse events whose nature or intensity is not in accordance with any adverse event expected, will be reported by the researcher to the study coordinator by telephone, mail or fax as soon as is reasonably possible, but in any case within 24 hours of occurrence.

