## Background

Fragile X syndrome (FXS) was first described by Martin and Bell in 1943 in families with several males affected by sex-linked mental retardation [1]. It later was identified as the most common cause of inherited mental retardation [2–4]. The prevalence of FXS has been estimated at 1 in 2,500 males and 1 in 4,000 females [5, 6].

In addition to moderate to severe mental retardation, individuals with FXS exhibit macroorchidism—an elongated face, long ears, connective tissue dysplasia, hyperactivity, autistic-like and stereotypical behaviours, speech delay and increased sensory sensitivity [7, 8]. Neuropathological features of FXS are a long, thin, tortuous appearance of cortical dendritic spines, increased intracranial volume, enlarged ventricles, increased volume of selective subcortical grey-matter regions and decreased size of the posterior cerebellar vermis [9], and, in a mouse model, altered glucose metabolism [10].

The name *fragile X syndrome* came into existence upon the discovery of a fragile site in the long arm of the X chromosome detected by cytogenetic testing in a cell culture medium deprived of folic acid [11]. The fragile X mental retardation 1 (*FMR1*) gene was linked to the region (Xq27.3), and a dynamic CGG repeat expansion mutation was identified as the cause of the syndrome [12]. A full mutation with more than 200 CGG repeats causes methylation of *FMR1* and leads to transcriptional silencing of the gene [13]. It has been established that a normal range of CGG repeats varies between 6 and 55, and a CGG expansion over this range is considered abnormal. An unstable premutation allele consists of more than 55 CGG repeats, resulting in reduced levels of the fragile X mental retardation 1 protein (FMRP) encoded by *FMR1*, despite a larger quantity of its mRNA. This may be due to a compensatory mechanism derived from a translation problem in the premutated mRNA [14]. A late-onset neurodegenerative disorder that causes intention tremor, problems with coordination and balance (cerebellar ataxia) and cognitive disability has been described in males and females older than 50 to 55 years of age who are carriers of a premutation allele. This disorder is known as fragile X premutation tremor/ataxia syndrome, which is caused by an increased level of mRNA that leads to neurotoxicity in the brain [15].

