## Methods/Design

We designed a clinical trial to evaluate the effects of an antioxidant combination of ascorbic acid and α-tocopherol on the clinical condition of patients with FXS. The study includes patients from age 6 years up to age 18 with diagnosed FXS. This age limit was chosen because it is within this age range that a decline in hyperactivity and behavioural symptoms may occur. The minimum duration of treatment and follow-up for these patients is to be 6 months. The symptoms most easily measured are the presence and severity of behavioural abnormalities.

Here we present a new therapeutic approach to FXS that is based on the hypothesis that an increase in free radical production and a deficit in vitamins are involved in the pathology and that this often provokes severe comorbidity. Moreover, we take into account that current treatment protocols are frequently ineffective among young children and carry a risk for important potential side effects. Thus, we propose the following goals. (1) Our main goal is to test whether the combination of 10 mg/kg/day α-tocopherol and 10 mg/kg/day ascorbic acid reduces hyperactivity and behaviour abnormalities, improving cognition among patients between 6 and 18 years of age compared to placebo treatment. (2) Secondary goals are to assess the safety of the treatment, in terms of adverse events; to describe metabolic changes resulting from the treatment, as revealed by blood test results; and to measure the impact of this treatment on the quality of family and social life.

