**Clinical trial flowchart.**

### Study subjects

Male patients ages 6 to 18 years with a diagnosis of FXS and clinical and behavioural symptoms of the disorder will be recruited.

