#### General considerations

A descriptive statistical analysis will be performed using statistics of central trend and dispersion for the quantitative variables and frequency distributions for the categorical variables carried out separately for the experimental and control groups. The baseline variables will be compared using these techniques. A flow diagram will be drawn to show the sequence from the initially eligible population to those excluded from the study (refusals, dropouts, lost to follow-up and so forth) in accordance with the criteria in the CONSORT guidelines.

A comparison will be made of between-group differences in the initial and final measurements for the diverse elements of the CPRS-R, CTRS-R and DBC-P24 using unpaired nonparametric tests. For the final within-group comparison, paired nonparametric tests will be used for nonparametric repeated measures with adjustments for baseline imbalances and scores. The same analysis will be performed for the index of psychological well-being to measure the repercussions of the treatment on family life.

The principal outcome variable (POV) will be taken as the change in global score on the Conners scales, adjusted for the baseline values. A simple linear regression model will be constructed for this POV, and the level of significance will be set at *P* < 0.05. Subsequently, a multiple linear regression model will be created, including the variable ‘Experimental/Control Group’ and adjusting for any baseline variables that may be unbalanced. Statistical adjustment will be performed by means of a multivariate model including the variable group (experimental and control) and concomitant treatment (yes or no). The safety of the treatment will be described in terms of the percentage of adverse effects.

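### The adverse-event rule relies on spontaneous report by the subject or staff observation; no section names the parent as a reporter or says that events are asked about

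*Protocol article*

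**What the plan says.** **The capture rule.** Reporting of adverse events states: "Any adverse events reported spontaneously by the subject or observed by the researcher or the research team will be recorded". The rest of that section deals with grading, periodicity, causality and expedited reporting once an event is known. It gives no other route by which an event becomes known.

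**What depends on it.** Methods/Design says: "Secondary goals are to assess the safety of the treatment, in terms of adverse events". General considerations, under Data analysis, says: "The safety of the treatment will be described in terms of the percentage of adverse effects".

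**Who is treated, and where.** Study subjects: "Male patients ages 6 to 18 years with a diagnosis of FXS and clinical and behavioural symptoms of the disorder will be recruited". The Background opens its clinical description with "In addition to moderate to severe mental retardation, individuals with FXS exhibit" and lists speech delay in the same sentence. Dosage and administration of medication: "The medication used in the trial will be administered orally at the patients’ homes".

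**Planned contacts.**
- Instrumentation: "a phone call follow-up is to be performed by the same neuropsychologist in charge of the evaluation at 30, 60, 120 and 150 days". What is asked on these calls is not stated.
- Follow-up of patients who withdraw from the study: reports at days 15, 30, 60 and 90 for everyone who received medication or placebo. Their content is not stated.
- Study periods: assessments at 12 weeks (t1) and 24 weeks (t2), with rating scales, blood and urine tests.
- Safety evaluation: an extensive laboratory panel and a list of medical parameters.

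**The concern.** A rule that waits for the subject to volunteer a complaint works best in patients who can recognise a symptom, connect it with a treatment and say so. The Background describes a condition in which many boys will find this hard, and enrolment starts at age 6. The mild and moderate grades in the adverse-event section turn on discomfort, which is a subjective report.

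The second route, observation by staff, needs staff to be present. Treatment is given at home, and the assessments after baseline are at 12 and 24 weeks. A symptom that begins and ends at home between contacts is most likely to be noticed by a parent, and the rule does not mention parents. Elsewhere the article does name other informants: parents and teachers for the Conners scales, parents for the well-being index.

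At stake is the secondary safety aim. Its stated summary is a percentage of adverse effects, so an event that is not captured lowers it directly. The rule that serious or unexpected events reach the coordinator within 24 hours of occurrence also presupposes a route from the family to the researcher, and none is described.

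**Working it through.** The plan gives no adverse-event rate and no capture share, so there is no figure of its own to reproduce. The check has a textual part and an illustration.

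**1. Is there an active route anywhere in the text?**

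| Contact | Section | Informant for adverse events named? | Events said to be asked about? |
|---|---|---|---|
| Calls, days 30, 60, 120, 150 | Instrumentation | No | No |
| Reports, days 15, 30, 60, 90 | Follow-up of patients who withdraw from the study | No | No |
| t1 and t2 | Study periods | No | No |
| Blood and urine tests | Safety evaluation; Study periods; Discussion | Not needed | Not needed: staff see the results |

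The stated rule is thus passive, and nothing elsewhere in the article supplements it for symptoms. Laboratory abnormalities do not depend on it.

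**2. What partial capture would do.** Inputs: 15 patients per group (Calculation of statistical power, establishment of sample size and safety). Assumed, because the document gives neither: true probability p that a patient has an event, and share c of such events that is recorded. Patients are taken as independent.

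Expected number recorded = 15 × p × c. Chance of recording at least one = 1 − (1 − p × c)^15.

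With p = 10%:
- c = 100%: 1 − 0.900^15 = 79%
- c = 75%: 1 − 0.925^15 = 69%
- c = 50%: 1 − 0.950^15 = 54%
- c = 25%: 1 − 0.975^15 = 32%

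With p = 20%, the expected numbers recorded at the same four values of c are 3.0, 2.25, 1.5 and 0.75, and the chances of recording at least one are 96.5%, 91.3%, 79.4% and 53.7%. With p = 30%, the chances are 99.5%, 97.8%, 91.3% and 68.9%.

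**3. Effect on the comparison of arms.** If c is the same in both arms, the recorded difference is c × (p1 − p2), while the ratio (c × p1)/(c × p2) = p1/p2 is unchanged. For assumed true rates of 40% and 10%, the difference is 30 percentage points at full capture and 0.5 × 30 = 15 points at half capture. Power at 15 per arm, already low at 47%, falls to 23%.

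**The case against.** The strongest reply is that the article condenses a longer protocol, and that call scripts and event forms are details an article normally leaves out. The section mentions a purpose-made form that is not shown. The calls may well include a question about events; their content is unstated, which is not the same as excluding it. The word subject may also be meant to cover the parent: the article elsewhere has patients withdrawing from the study although parents give consent, and the severity wording (incapacity to work) reads like a template. All of this stands as a reason for caution about practice. It does not remove the point, because the article does not stay silent on how events are captured. It states a rule, and that rule names two passive routes.

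The reply is also right that the trial has other eyes on safety. Blood and urine are tested at t0, t1 and t2, partly to corroborate safety. Parents complete behaviour scales at t1 and t2, so worsening behaviour would not go wholly unseen. The possible gap is therefore confined mainly to symptomatic events at home between contacts.

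Four stronger readings are tempting, and the document does not support them:
- *Events count only if the child himself reports them, and parents are excluded.* The text names neither the child nor an exclusion; it simply does not name the parent.
- *Staff have contact on only 2 of the 168 days (24 × 7) after baseline.* This counts clinic assessments alone and leaves out the calls and the follow-up reports.
- *Zero events would be compatible with a true rate of 36%.* With no events in 15 patients, the one-sided 95% upper limit is 1 − 0.05^(1/15) = 18.1%. That reflects the sample size and holds under perfect capture. Dividing by 0.5 to reach 36% rests entirely on an assumed capture share.
- *The rule favours the active arm.* Under blinding, equal under-capture lowers both percentages and leaves their ratio alone.

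**Conclusion.** The point holds as a weakness in a stated rule. The rule depends on spontaneous report by the subject or observation by staff. No section adds the caregiver as a reporter or says that events are asked about. Given home treatment and the condition as the Background describes it, under-recording of symptomatic events at home is likely. It is not demonstrated, and a reader should not infer that the safety aim is bound to fail.

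The consequence would be lower percentages in both arms and a smaller absolute difference. Its size cannot be obtained from the document. The illustrative fall from 79% to 54% or 32% in the chance of seeing even one event rests on an assumed true rate of 10% and assumed capture shares of 50% and 25%. For a descriptive secondary aim in a 30-patient pilot, this is an inexpensive improvement worth making; it does not put the trial's primary result in doubt.

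**What to change.** In Reporting of adverse events, name the parent or guardian as a reporter alongside the subject. State that the same open adverse-event question is put to the parent or guardian at every scheduled call (days 30, 60, 120 and 150) and at t1 and t2, in both arms, in addition to spontaneous reports and staff observation.

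That gives 4 + 2 = 6 occasions per patient after baseline. With t1 at day 84 and t2 at day 168, the longest interval between them is 120 − 84 = 36 days. Since the caller is also the evaluator, the wording should be fixed in advance and identical for every patient.

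The cost is one standard question at contacts that already take place; the small downside is more minor events to record. No change to the safety summary in General considerations is needed for this point.
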